**5.8 Trial oversight:**

The steering committee of the study will include, except for the PI, two other Infectious Disease physicians ([name] and [name]). There will be biweekly discussions of the progress

report, reporting of compliance with active surveillance, reporting of compliance with

bathing, and any adverse reactions or other problems.

**5.9 Statistical analyses**

Changes in the rates of BSI and clinical sepsis will be compared between the intervention and the control period. Continuous variables will be examined with the use of two-sample t-tests and linear regression modeling, and categorical variables will be examined by means of Fisher’s exact test. Cox proportional-hazards regression model will be used to compare the time from admission until the first primary bloodstream infection , clinical sepsis or acquisition of MDRO between the control and intervention periods.

**Sample size calculation:** based on our ongoing surveillance, there are 2-3 BSI events per 1000 patients –days in our NICU. In order to detect a 50% reduction in BSI rates , we will need 37,096 patient days (18,548 in each group) in order to have 80% power to reject the null hypothesis, with 0.05 level of significance. Currently, our average annual census is 45,000 patient days. therefore, a 2-year study will have >80% power to reject the null hypothesis (the BSI rates in the control period equal the rates in the intervention period).

**For the preliminary study, we used the data in Milstone et al. ^18^ who reported no serious adverse skin reactions and an incidence of 1.2 minor skin reactions per 1000 patient days. A sample of 500 patient days will enable us to detect a ten-fold higher rate of minor skin reactions. Therefore at least 200 patient days in each group of the preliminary study (>600 patient days), would suffice.**

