**TBD**

3. Background

Preterm delivery rates in developed countries, including Israel, vary between 5-11%^[[1]](#endnote-1),^^[[2]](#endnote-2)^. Nosocomial infections (NIs) are a major health problem among premature infants, and are associated with increased morbidity, mortality, length of hospital stay, and costs^[[3]](#endnote-3),^^[[4]](#endnote-4)^. Overall infection rates range from 8.9 to 62 infections per 1,000 patient days^[[5]](#endnote-5)^’^[[6]](#endnote-6)^. Over the last 25 years, the improvement in survival of premature infants was paralleled by an increased rate of nosocomial infections (NI), especially among very low birth weight (VLBW) infants, who develop NI in 21-43% of cases^3^. This incidence is inversely related to gestational age and birth weight and directly correlated with severity of illness, length of stay, ventilation, central catheters, parenteral nutrition days, and broad spectrum antibiotics.

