**5.5 Intervention**

All infants in the NICU eligible for the study will be assigned for bathing three times a week with washcloths impregnated with 2% chlorhexidine gluconate (Clinell ® Chlorhexidine wash cloths, GAMA healthcare) during the initial 6-months study period (intervention), followed by standard bathing during the second 6-months period, then again intervention period for 6 months and standard bathing for 6-months. Total study period- 2 years.

**Inclusion criteria**: infants weighing ≥1500 grams and ≥10 days of age; parents’ informed consent

**Exclusion criteria:** infants weighing <1500 grams or <10 days of age**;** parents’ refusal to sign informed consent.

For standard bathing procedure see appendix 1.

Before the study initiation, as well as at the beginning of each study period, nurses will be instructed on the proper technique for bathing patients. Bathing will be performed according to product brochure, three times a week.

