**5.6 Outcome measures**

A. Number of BSI/CLABSI/clinical sepsis events per 1000 patient days during the intervention periods compared with the control periods.

B. Number of new patients colonized with MRSA, VRE, CRAB or ESBL per total number of patients, monthly range and variance.

C. Number of new patients colonized with MRSA, VRE, CRAB or ESBL per 1000 eligible patient days [ Total patient days – total patient days for patients identified with MDRO]

D. Time to colonization with MDRO during the intervention periods compared with the control periods.

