**5.7 Data collection**

Each patient admitted to the NICU during the study periods and meeting the inclusion criteria, will be recorded and assigned a specific study number. The dates of admission and dates of discharge will be recorded and used to calculate length of stay and to determine the

incidence of nosocomial infections based on microbiological data. Clinical and laboratory data, including the use of invasive device (intravascular devices, mechanical ventilation, feeding tubes) will be collected on standardized forms. The data will be coded under a password protected database and linked only to study patient identifier.

Infections and MDRO acquisitions will be monitored during the study period. Events occurring within 2 days after the transition will be assigned to the previous bathing period.

For infection surveillance, daily review of cultures and new orders for antibiotic therapy will be performed for all study participants. Infectious events will be evaluated by an independent investigator blinded to the intervention period.

Active surveillance testing for MDRO will be performed once every two weeks during the study period. Swabs from the nasopharynx (for MRSA)] and from the rectal area (for ESBL producing organisms, VRE and CRAB) will be obtained by unit staff and processed in the microbiology laboratory of Shaare-Zedek Medical Center.

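### Section 5.9 compares infection rates between non-randomised calendar periods and names no adjustment for case mix, although the protocol names the risk factors and holds data on them

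*Protocol*

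**What the plan says.** Section 5.5 of the protocol assigns chlorhexidine bathing to the first 6 months, "followed by standard bathing during the second 6-months period, then again intervention period for 6 months and standard bathing for 6-months". The order is fixed, there is one unit, and nothing is randomised.

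Section 5.6 defines the leading outcome measure as "Number of BSI/CLABSI/clinical sepsis events per 1000 patient days during the intervention periods compared with the control periods". Section 5.9 gives the analysis: "Changes in the rates of BSI and clinical sepsis will be compared between the intervention and the control period". It adds t-tests and linear regression for continuous data, Fisher's exact test for categorical data, and a Cox model that compares time to first event between control and intervention periods. None of these is given a covariate.

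On risk, section 3 (Background) says of nosocomial infection that "This incidence is inversely related to gestational age and birth weight and directly correlated with severity of illness", and continues the list with "length of stay, ventilation, central catheters, parenteral nutrition days, and broad spectrum antibiotics". On data, section 5.7 states that "Clinical and laboratory data, including the use of invasive device (intravascular devices, mechanical ventilation, feeding tubes) will be collected on standardized forms". Weight is an entry criterion in section 5.5, and Appendix 1 sets the standard bath by gestational age, so both are known for each infant. Section 5.9 gives none of these data a role.

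**The concern.** In a randomised trial, an unlisted covariate set mainly costs precision, and leaving it to an analysis plan is normal. Here the calendar decides which bath an infant receives, and nothing balances risk between the two conditions. If the chlorhexidine blocks happen to hold fewer ventilated or catheterised infants, a period-only comparison attributes their lower rate to chlorhexidine. If they hold more, a real benefit is diluted.

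Parental consent is a second possible route to imbalance. Parents are asked when the block in force already fixes the bath, so the enrolled mix could differ between blocks even if admissions do not. The protocol does not show that this happens.

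The expected event count is small, so a modest bias matters beside the sampling error. A larger study would not cure it: the standard error shrinks and the bias does not.

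**Working it through.** **The plan's own figure.** Section 5.9 asks for 18,548 patient-days per group for 80% power, 5% significance and a 50% reduction, with a control rate of 2 to 3 per 1000. A plain two-proportion formula at 2.5 versus 1.25 per 1000, two-sided, gives 18,801 per group, 1.4% above the stated figure. At 2 per 1000 it gives 23,511 and at 3 per 1000 it gives 15,662. The stated size is thus consistent with an unadjusted two-group comparison at the midpoint rate.

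**Inputs from the protocol.** 18,548 days per group; control rate 2 per 1000 (2.5 as a check); about 800 infants, taken as 400 per condition; census of 45,000 days a year.

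**Assumed inputs (not in the protocol).** High-risk infants have k = 2, 3 or 4 times the BSI rate of the others. They supply a share pC = 40% of control days and a share pI of chlorhexidine days. The test is two-sided at 5%.

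**Formulas.** With no true effect, the crude rate ratio is

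RR = (pI·k + 1 − pI) / (pC·k + 1 − pC).

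Expected control events are E0 = 18,548 × 0.002 = 37.1, and E1 = E0 × RR. The standard error of log RR is √(1/E0 + 1/E1). The chance of a significant result in favour of chlorhexidine is Φ(−ln RR / SE − 1.96), which is 2.5% when RR = 1.

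**How large is a chance shift?** The standard error of the difference between two 40% shares with 400 infants each is √(2 × 0.4 × 0.6 / 400) = 0.035, or about 3.5 points. If unequal stays doubled the variance (an assumption), it would be 4.9 points. A shift of about 4 points is therefore chance-sized. A 10-point shift is 2.0 to 2.9 standard errors and would normally need a systematic cause.

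**Worked case, k = 2, 40% versus 36%.** RR = (0.72 + 0.64)/(0.80 + 0.60) = 1.36/1.40 = 0.971; E1 = 36.0; SE = 0.234; Φ(0.029/0.234 − 1.96) = 3.3%.

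| High-risk share, control vs chlorhexidine | Spurious RR, k = 2 / 3 / 4 | One-sided error at 2 per 1000 | at 2.5 per 1000 |
|---|---|---|---|
| 40% vs 40% | 1.00 | 2.5% | 2.5% |
| 40% vs 36% | 0.97 / 0.96 / 0.95 | 3.3 / 3.9 / 4.3% | 3.4 / 4.1 / 4.5% |
| 40% vs 30% | 0.93 / 0.89 / 0.86 | 5.0 / 7.1 / 8.8% | 5.4 / 7.9 / 10.0% |

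**Opposite direction.** With 30% of control days and 40% of chlorhexidine days at high risk, the spurious RR is 1.08 / 1.13 / 1.16. Power for a true halving at 2 per 1000 falls from 68% to 61 / 56 / 52%.

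**More data.** The census over 2 years allows at most 45,000 × 2 / 2 = 45,000 days per condition, before eligibility and consent. At that size and 2 per 1000, the 40% versus 30% shift gives an error of 7.1 / 11.6 / 15.6%.

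**The case against.** The strongest reply is that section 5.9 does not say the comparison is unadjusted. It says that rates will be compared, and it names linear and Cox regression, both of which can carry covariates. Covariate lists are often left to a statistical analysis plan, which is not at hand. This stands in part: that the comparison is crude is inferred from the absence of any adjustment. It does not dispose of the point. With a non-randomised contrast, adjustment decides whether the estimate is protected from measured confounding, and the only contrast that the protocol states is by period.

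Three further objections stand and limit the size.

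- The risk statement in section 3 is about premature infants, with emphasis on those of very low birth weight. Section 5.5 excludes infants below 1500 g and under 10 days old, so the gradient among eligible infants may be weaker than the assumed 2 to 4.
- Alternating four blocks in one unit reduces the effect of a steady trend.
- The event counts used here are for BSI alone, whereas the primary outcome also includes clinical sepsis. More events would shrink the standard error and leave the bias unchanged.

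A reader might infer that the trial will report a case-mix shift as a chlorhexidine effect, or that the error reaches the 9 to 24% that a 20-point shift (40% versus 20%) would give at 2 per 1000. The protocol supports neither. It shows no shift, a shift could go either way, and 20 points is 4.1 to 5.8 standard errors on the reckoning above.

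**Conclusion.** The point holds in a limited form. As written, section 5.9 contrasts non-randomised periods with no adjustment named, while the protocol itself identifies the risk factors and holds data on several of them. If case mix differs between periods, the estimate is confounded in the direction of the difference.

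The size cannot be known from the protocol. Under the assumed 2- to 4-fold risk, 2 per 1000 and 18,548 days per group, a chance-sized shift of 4 points is a small matter: a ratio of about 0.95 to 0.97 and an error of about 3 to 4%. A systematic 10-point shift is not: 0.86 to 0.93 and about 5 to 9%.

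It would be tempting to read the power figures as a promise that adjustment wins back 8 to 16 points (68% against 61 to 52%). That would require one fully measured factor, perfect removal of its effect and no loss of precision, none of which the documents support. Nor can covariates remove unmeasured differences. If the 6-month blocks run consecutively, both chlorhexidine blocks fall in the same half of the year, so season cannot be separated from treatment by any model.

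**What to change.** In section 5.9:

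- Make the primary comparison a Poisson or negative binomial regression of events on bathing method, with patient-days as offset.
- Adjust for a few values fixed at entry to each bathing period: gestational age, weight, central catheter (yes/no) and mechanical ventilation (yes/no), or one baseline risk score built from them. Defining entry per bathing period also covers infants whose stay spans a transition. Later device use should stay out of the model, because it can result from an infection.
- Report the crude rate ratio beside the adjusted one, and use the same covariates in the Cox model.
- Tabulate case mix for each of the four blocks.
- State that adjustment removes measured imbalance only, and that with consecutive blocks season is not separable from treatment.

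The cost is wording and a little more analysis, with no new patients or visits. Device use is already collected, and weight and gestational age are already known. Device status must be dated so that its value at entry can be read off. The downside is a few extra model terms on limited events: about 37 + 19 = 56 BSI at 2 per 1000 with a true halving, which is why the list should stay short.

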The emergence of multidrug- resistant organisms (MDRO) in acute-care settings, including the neonatal intensive care unit (NICU) , complicates the antimicrobial therapy and highlights the urgent need to limit the spread of such organisms and reduce the rate of NIs. Resistant organisms such as methicillin-resistant *Staphylococcus aureus* (MRSA), extended-spectrum beta-lactamase producing enterobacteriacae (ESBL) and carbapenem resistant *Acinetobacter baumanii* (CRAB) have caused outbreaks with associated morbidity and mortality in NICUs around the world ^[[7]](#endnote-7)^’^[[8]](#endnote-8)^’^[[9]](#endnote-9)^ . A stay in the NICU for > 1 week is a prominent predictor of colonization with resistant organisms^[[10]](#endnote-10)^. Strategies that have been utilized to limit the spread of MDRO within ICU’s have included stricter attention to barrier precautions following identification of patients colonized with these organisms, as well as improved handwashing. One prominent strategy that has emerged as recommended by recent SHEA guidelines ^[[11]](#endnote-11)^suggests that hospitals should adopt more aggressive active surveillance culturing to identify patients colonized with MDRO at the time of admission and periodically during their hospital stay. It is advocated, that under this “search and isolate” strategy, once reservoirs of resistant organisms within the hospital are identified, nosocomial transmission can be effectively eliminated through the use of strict barrier precautions and hand hygiene for these previously unidentified patients. However, this “search and isolate” strategy has multiple flaws. First, it is costly and requires high level of compliance with contact precautions and hand hygiene among healthcare personnel. Second, this strategy does little to eradicate colonization.

*As long as patients remain colonized, the opportunity for transmission exists. Therefore, a strategy that may address skin carriage of pathogens has the potential to reduce horizontal transfer to other patients as well as reduce the colonized patient’s risk to develop infection.*

The guidelines for preventing intravascular catheter-related infections published by the Centers for Disease Control and Prevention (CDC) recommend daily skin cleansing of ICU patients with 2% chlorhexidine to reduce catheter-related bloodstream infections (BSI)^[[12]](#endnote-12)^, but could not recommend its use in infants < 2 months of age due to lack of safety and efficacy data.

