**4. Expected significance**

National data from the USA indicate that almost a quarter of very low birth weight infants will have one or more episodes of sepsis. Compared with infants without sepsis, infants with sepsis had a significantly longer hospital stay (79 vs.60 days), had a 2-fold increase in the number of days on mechanical ventilation, and had a significantly higher mortality rate (18% vs 7%)3. Another American study estimated that, on average, the cost of NICU care was $16,800 greater per infant who experienced NICU-associated BSI^[[32]](#endnote-32)^. Approximately 7% of infants, or >12,000 infants, are born prematurely in Israel every year^[[33]](#endnote-33)^. Extrapolating the American data to the Israeli NICU translates into a major health problem. The Ministry of Health and the Israel Neonatal Society have recently launched a national program aimed at minimizing the rate of NI in the Israeli NICUs^33^. In our NICU we have adopted this program and have increased staff education, active monitoring of compliance with guidelines, as well as adoption of the “search and isolate” policy, with twice a week screening of patients for colonization with MDRO.

Despite these measures, BSI rates remain high in our NICU, which prompt us to search for additional interventions such as CHG baths. The goal of the currently proposed study is to determine if universal use of a chlorhexidine based bathing system for patients in the NICU will decrease skin bacterial burden and lead to decreased horizontal transmission of MDRO.

Additionally, we hypothesize that reduced skin colonization with opportunistic bacterial

pathogens will result in a reduction in the rate of CLABSI, BSI and clinical sepsis in comparison to regular bathing procedures.

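### Section 5.9 tests MDRO acquisition as if infants acquire independently, although the hypothesis is spread between them, so chance clusters can give a false significant benefit or harm on these secondary outcomes

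*Protocol*

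**What the plan says.** Section 5.9 sets two methods that bear on MDRO acquisition.

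- **Cox regression, explicitly.** It compares the time from admission to a first bloodstream infection, "clinical sepsis or acquisition of MDRO between the control and intervention periods". This serves outcome D in section 5.6: "Time to colonization with MDRO during the intervention periods compared with the control periods".
- **Fisher's exact test, by inference.** Section 5.9 says that "categorical variables will be examined by means of Fisher"'s exact test, without naming MDRO. Outcome B, "Number of new patients colonized with MRSA, VRE, CRAB or ESBL per total number of patients, monthly range and variance", is a per-infant yes/no outcome, and no other test is offered for it.

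Outcome C, new colonisations per 1000 eligible patient-days, is a rate. Section 5.9 assigns no test to it.

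Section 5.9 mentions no clustering, overdispersion, robust variance, or period or calendar term. Outcome B asks for a monthly variance, but section 5.9 does not use it in any comparison.

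The premise is stated elsewhere. Section 4 asks whether chlorhexidine bathing "will decrease skin bacterial burden and lead to decreased horizontal transmission of MDRO". Section 3 says that colonised patients are a source for others and that resistant organisms "have caused outbreaks with associated morbidity and mortality in NICUs around the world". Sections 5.3 and 5.5 put the whole study in one NICU, with four alternating six-month periods that start with chlorhexidine.

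**The concern.** The null distributions of Fisher's test and of the usual Cox test assume that each infant's acquisition tells us nothing about the next infant's. The protocol assumes the opposite: one colonised infant raises the risk of those nearby. Acquisitions then arrive in clusters, and the count in a period varies more than independence allows.

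Because the whole unit is on one bathing method at a time, a cluster falls largely inside one condition and does not average out. With equal true rates, an outbreak in one six-month period can look like a treatment effect. P-values would be too small and confidence intervals too narrow on the outcomes that measure the transmission hypothesis most directly. Better handling of patient-days or period membership would not remove this.

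**Working it through.** **The plan's own figure.** Section 5.9 sizes the trial for BSI only, so no MDRO figure can be reproduced. The stated 18,548 patient-days per group follows from the Poisson two-rate formula n = (z_α + z_β)²(r₁ + r₂)/(r₁ − r₂)², with rates of 2 and 1 per 1000 and a one-sided 0.05: (1.645 + 0.842)² × 0.003/0.001² ≈ 18,548. It too assumes independent events. The point below does not depend on it.

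**Inputs.** About 800 infants (synopsis); four six-month periods, two per condition (section 5.5); nominal level 0.05 (section 5.9). Assumed, because the protocol does not give them: 400 infants per condition, 10% acquiring (5% to 20% as a range), and the cluster sizes below.

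**Closed form.** If acquisitions come in clusters of size S, the variance of a period count is inflated by V = E[S²]/E[S]. For fixed clusters, V = m. For geometric sizes with mean m, E[S²] = 2m² − m, so V = 2m − 1. The actual error of a nominal two-sided 5% test is 2(1 − Φ(1.96/√V)).

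| Mean size (geometric) | V | Actual error |
| --- | --- | --- |
| 1 | 1 | 5.0% |
| 1.5 | 2 | 16.6% |
| 2 | 3 | 25.8% |
| 3 | 5 | 38.1% |

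The error doubles to 10% when 1.96/√V = 1.645, that is V = (1.96/1.645)² = 1.42.

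**Simulation of Fisher's test, no true effect, 10% acquiring.** The error was about 4–5%, 14–17%, 21–26% and 28–37% at mean sizes 1, 1.5, 2 and 3. It is lower when members of a cluster are spread over time, so that some cross a period boundary. Results at 5% and 20% acquiring were similar.

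**Day-by-day transmission model, no true effect.** 800 infants, mean stay 25 days, four alternating 182-day blocks, 8–9% colonised. The log-rank test stands for the Cox score test.

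| Spread | Fisher | Log-rank |
| --- | --- | --- |
| none | 4.0% | 5.7% |
| moderate | 23.7% | 26.0% |
| strong | 43.5% | 46.7% |

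**Direction.** False rejections split evenly. With fixed clusters of three, 13.0 of 26.1 percentage points favoured chlorhexidine.

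**What repairs it.** A quasi-Poisson comparison of block counts (dispersion at least 1, t reference) was run on the same kinds of data.

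- *Monthly blocks.* If every cluster stays inside one month, the error is 2–5%. If successive cases are 7–14 days apart, it is about 6–12% at mean sizes 1.5 to 3. In the day-by-day model, 26-day blocks cut the error of an independence-based rate comparison only from 24% to 11% (moderate spread) and from 47% to 18% (strong spread).
- *Three-month blocks.* Each six-month period holds two, giving 8 blocks and 8 − 2 = 6 degrees of freedom. With the same gaps the error stayed at or below 5%. With no transmission it was about 1%.
- *Four periods.* With 2 degrees of freedom (critical t 4.30) the error was at most 1%, with very little power.

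**The case against.** **Fisher is not named for MDRO.** Correct: only the Cox link is explicit. The inference is reasonable for outcome B. A reader might extend it to outcome C, but C is a rate per patient-days and section 5.9 gives it no test.

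**A variance estimator can be left to a statistical analysis plan.** This has force for the Cox model, since a robust variance would not contradict section 5.9. But section 5.9 names tests whose usual null conflicts with the stated mechanism. Followed as written, it gives p-values that are too small.

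**The size is assumed and may be high.** This also stands. Enrolment is limited to consented infants of at least 1500 g and at least 10 days, so some links in a chain are not counted. If half of each cluster is enrolled, Fisher's error at mean sizes 1.5, 2 and 3 falls to 11%, 19% and 24%. The unit's existing screening and isolation (section 4) may also keep clusters small. The error remains above 5% in all these cases.

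**A monthly overdispersion model would settle it.** A reader might infer this because outcome B already reports monthly variance. It holds only if chains stay within a month, and nothing in the protocol supports that. Section 5.7 samples MDRO status once every two weeks, so recorded cases in one chain can easily fall in different months.

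**Conclusion.** The point holds for outcome D explicitly and for outcome B by inference. The direction follows from the protocol's own premise. The size does not: roughly 14% to 37% in place of 5% rests on an assumed 10% acquisition and mean cluster sizes of 1.5 to 3, and is lower with incomplete enrolment of clusters.

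Two stronger readings are not supported. A reader might infer that the plan is tilted towards chlorhexidine, but about half the false rejections favour standard bathing. A reader might also infer that the main result fails. The outcomes at issue are secondary under section 5.2, and this argument does not touch the BSI comparison or its sample size.

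No model fully repairs a comparison made in one unit over four periods, so MDRO conclusions need cautious wording whichever analysis is used.

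**What to change.** In section 5.9:

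1. State that conclusions on MDRO will not rest on p-values that assume independent infants.
2. For outcomes B and C, compare acquisition counts per calendar block with a quasi-Poisson model: one term for bathing method, offset log eligible patient-days, dispersion not below 1, t reference distribution. Use blocks long enough to contain most transmission chains. Three-month blocks (8 blocks, 6 degrees of freedom) fit inside the six-month periods.
3. For outcome D, keep the Cox hazard ratio, give it a variance clustered on the same blocks, and label it supportive. With one unit, four periods and so few blocks, this variance is itself only approximate.

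The change is to wording only. It needs no more infants, and the acquisition and patient-day data are already collected for outcomes B and C. The price is wider intervals, lower power, and a conservative test (about 1% error) if there is in fact no transmission.

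### The 37,096 patient-days match a one-sided 5% calculation at 2 versus 1 BSI per 1000, but no one-sided test or base rate is declared; two-sided power is about 70% to 86% over the stated 2–3 per 1000

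*Protocol*

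**What the plan says.** The sample size paragraph in protocol section 5.9 gives these inputs:

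- Base rate: "there are 2-3 BSI events per 1000 patients"-days, as a range. The value entered in the calculation is not named.
- Effect: "In order to detect a 50% reduction in BSI rates".
- Error rates: "with 0.05 level of significance" and 80% power. Whether the level is one-sided or two-sided is not said.
- Null hypothesis: "the BSI rates in the control period equal the rates in the intervention period".
- Result: "we will need 37,096 patient days (18,548 in each group) in order to have 80% power to reject the null hypothesis".

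The paragraph then cites a unit census of 45,000 patient-days a year and concludes that two years will give more than 80% power. Section 5.5 fixes the duration at four alternating six-month periods. It restricts the study to infants of at least 1500 g and at least 10 days of age whose parents consent.

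**The concern.** A 0.05 level set against a null of equal rates, with nothing said about direction, will normally be read as a two-sided test. If the figure was worked out one-sided, the sample size and the power stated beside it do not belong together under that reading.

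The figure matters because it is the only number in the protocol against which accrued patient-days can be judged sufficient. Someone who compares enrolled days with 37,096 and then reports a two-sided p-value would believe that the study has 80% power when, at the lower end of the protocol's own rate range, it has less.

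**Working it through.** **Formula.** For two Poisson rates r1 and r2 with equal exposure n per group:

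n = (z_α + z_β)² × (r1 + r2) / (r1 − r2)²

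With a 50% reduction, r2 = r1/2, and this simplifies to n = 6 (z_α + z_β)² / r1. For 80% power, z_β = 0.8416.

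**Reproducing the stated figure.** Take r1 = 0.002, r2 = 0.001 and one-sided 0.05, so z_α = 1.6449. Then (z_α + z_β)² = 6.18256 and n = 6.18256 × 0.003 / 0.001² = 18,547.67. This rounds up to 18,548 per group, or 37,096 in total, an exact match.

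Other methods were tried one-sided and two-sided at 2, 2.5 and 3 per 1000: two proportions with and without continuity correction, log rate ratio, arcsine, and the Schoenfeld and Freedman event formulas. None gave 18,548. The nearest one-sided alternative, two proportions at 2 versus 1, gives 18,519.

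**Two-sided 0.05.** Now z_α = 1.9600 and (z_α + z_β)² = 7.8489. Power at n = 18,548 is Φ[(r1 − r2)/√((r1 + r2)/n) − 1.9600]. At 2 per 1000, for example, this is Φ(2.4865 − 1.9600) = Φ(0.5265) = 70.1%.

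| Base rate per 1000 | Needed per group | Needed in total | Power at 18,548 per group | Same, exact conditional test |
|---|---|---|---|---|
| 2 | 23,547 | 47,094 | 70% | 67% |
| 2.5 | 18,837 | 37,675 | 79% | 77% |
| 3 | 15,698 | 31,396 | 86% | 84% |

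**Base rate at which 18,548 gives 80% two-sided.** r1 = 6 × 7.8489 / 18,548 = 0.00254, or about 2.54 per 1000. The lower half of the stated range falls short.

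**Gap at 2 per 1000.** 47,094 − 37,096 = 9,998 patient-days, which is 27% of the stated figure.

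**Against the census.** Two years at 45,000 is 90,000 patient-days, or about 45,000 per condition. If all were analysed, two-sided power at 2 per 1000 would be Φ(0.001/√(0.003/45,000) − 1.9600) = Φ(1.913) = 97%. The share of the census that must be eligible and enrolled is 37,096/90,000 = 41% for the stated requirement, and 47,094/90,000 = 52% for the two-sided requirement at 2 per 1000.

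**The case against.** **The census covers the gap.** A reader might infer that the trial as planned is underpowered. The protocol does not support that. The trial runs for a fixed two years, no rule ends it at 37,096 patient-days, and the census is nearly twice the corrected two-sided requirement. The 9,998-day gap lies between two formula results; it is not a deficit in planned accrual. This largely stands, with one limit: the census is that of the whole unit, while the analysed infants are a subset whose size is not given. The synopsis target of approximately 800 patients also suggests that the full census is not all study time. If 800 is the overall total, 90,000 days would be 112 per infant, against 46 for the stated requirement and 59 for the two-sided one at 2 per 1000. The choice between one-sided and two-sided decides whether the requirement at 2 per 1000 is met when the enrolled share lies between about 41% and 52%.

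**The 70% is the low end only.** A reader might take 70% as the power of the plan. It holds at 2 per 1000. A two-sided test at the midpoint of 2.5 needs 18,837 per group, within 1.6% of the stated figure. The exact match favours a one-sided origin at 2 versus 1, but that origin is inferred, since the protocol does not state the rate used. Only the range of 70–86% can be asserted without condition.

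**One-sided may have been intended.** An equality null is compatible with a one-sided alternative, and the synopsis endpoint and section 5.1 are both worded as a reduction. Sidedness could also be declared in an analysis plan that is not shown. So it is unstated, not contradicted. But the protocol has already fixed the number, and the reader cannot tell which test the 80% belongs to.

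**Conclusion.** The point holds as a moderate correction to a stated figure. The sample size of 37,096 patient-days with 80% power agrees exactly with a one-sided 0.05 test at 2 versus 1 per 1000, and neither that test nor that rate is declared. Read two-sided, its power is about 70% at 2 per 1000, 79% at 2.5 and 86% at 3, and the stated 80% is not met below about 2.54 per 1000.

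The conclusion of more than 80% power over two years is not overturned. It holds comfortably if the full census is analysed. At 2 per 1000 two-sided, it needs about 52% of the census to be eligible and consented, not 41%.

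All figures assume independent Poisson events, with no allowance for period or clustering effects. They concern BSI alone, whereas sections 5.2 and 5.6 also count clinical sepsis in the outcome, so they do not describe power for that broader outcome.

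**What to change.** In section 5.9, name the base rate used and state that the test is two-sided at 0.05. Then do one of the following:

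- Restate the requirement as 47,094 patient-days in total at 2 per 1000 (37,675 at 2.5; 31,396 at 3).
- Keep 37,096 and give its two-sided power as 70–86% over 2 to 3 per 1000.

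If a one-sided test was intended, say so explicitly; 37,096 then stands at 2 per 1000. In each case add that the calculation treats BSI events as independent and covers BSI only.

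The cost is about one sentence. Design, duration and conduct do not change; under the two-sided options, the stated figure or its power looks less favourable at the low end of the rate range.
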